## Abstract

**Background:**

Schizophrenia is a severe mental disorder affecting approximately 1% of the global population, characterized by three core symptom domains: positive symptoms, negative symptoms, and cognitive dysfunction. Repetitive transcranial magnetic stimulation (rTMS) has emerged as a promising intervention for both positive and negative symptoms in schizophrenia. However, its therapeutic potential for cognitive dysfunction remains inconclusive.

**Methods:**

This randomized, double-blind, sham-controlled trial will enroll 70 medication-stable patients meeting DSM-5 criteria for schizophrenia. Participants will be randomly allocated (1:1) to receive either active or sham augmented intermittent theta-burst stimulation (iTBS) targeting the left dorsolateral prefrontal cortex (DLPFC). The treatment protocol consists of 600 pulses per session, three sessions per day, for 10 consecutive weekdays. Clinical symptoms will be evaluated with the Positive and Negative Syndrome Scale (PANSS), cognitive function will be assessed using the Repeatable Battery for the Assessment of Neuropsychological Status (RBANS), and neural activity will be measured via functional near-infrared spectroscopy (fNIRS) during a semantic verbal fluency task. All patients will be assessed at baseline and post-intervention.

**Ethics and dissemination:**

The trial protocol complies with the principles of the Declaration of Helsinki and has been approved by the Ethics Committee of Zigong Mental Health Center (approval number: 20250802). The findings of this trial will be published and made publicly accessible in a peer-reviewed journal.

**Discussion:**

This study aims to provide strong evidence supporting the therapeutic potential of augmented iTBS for improving cognitive functioning in schizophrenia, offering a potential new treatment option for patients with schizophrenia.

**Clinical Trial Registration:**

https://www.chictr.org.cn/index.html, identifier ChiCTR2500107943.

## Introduction

1

Schizophrenia (SZ) is a chronic, highly disabling illness. The weighted lifetime prevalence of severe psychosis is 0.6% (1), characterized by three core symptom domains: positive symptoms (e.g., hallucinations, delusions), negative symptoms (e.g., affective flattening, social withdrawal), and cognitive dysfunction (particularly in social cognition and executive functioning) (2). Among these, cognitive dysfunction plays a key role in the long-term psychosocial impairment and disability experienced by patients with schizophrenia (3). Current antipsychotic medications demonstrate limited efficacy in alleviating negative symptoms and improving cognitive functioning (4). In recent years, repetitive transcranial magnetic stimulation (rTMS) has emerged as a promising therapeutic alternative. As a noninvasive brain stimulation technique, rTMS uses pulsed magnetic fields to induce targeted electrical currents in specific cortical regions, offering potential therapeutic benefits. While rTMS has demonstrated efficacy in treating depression and received Food and Drug Administration (FDA) approval for this indication in 2008 (5), its therapeutic effectiveness for schizophrenia remains controversial (6).

The mechanisms underlying cognitive impairment in schizophrenia remain elusive, with working memory deficits representing one of its most prominent features (7). Some studies have found that structural and functional abnormalities in the dorsolateral prefrontal cortex (DLPFC) may be closely linked to cognitive impairments in patients with schizophrenia. A neuroimaging study found reduced activation of DLPFC in patients with schizophrenia while performing working memory tasks (8). Magnetic resonance imaging (MRI) data have shown that reduced cortical thickness and grey matter volume in left DLPFC (L-DLPFC) of patients with schizophrenia (9), as well as reduced grey matter volume in the prefrontal lobe, are significantly associated with working memory deficits (10). Thus, functional abnormalities in the prefrontal lobes may underlie the neurological basis of working memory deficits in schizophrenia (11, 12).

A meta-analysis has shown that rTMS of L-DLPFC is effective in improving cognitive function, but the quality of evidence from these studies is not high (13). Currently, studies attempting to alleviate cognitive symptoms by stimulating the DLPFC have not yielded consistent results. Some studies have found that high-frequency (10 Hz) stimulation of L-DLPFC can improve patients’ cognitive functions (14, 15), especially facial expression recognition and social cognition (14). However, another study has shown that the stimulation has no significant effect on cognitive function (16).

In addition to the location of stimulation, the number of stimulation pulses may also be a key factor affecting efficacy. Recent studies have found that patients with depression who were initially unresponsive to rTMS showed improvement after receiving higher doses of stimulation (17). This suggests that the standard FDA-approved protocol may be underdosed. According to the latest clinical guidelines, the FDA-approved standard intermittent theta-burst stimulation (iTBS) treatment protocol provides 600 pulses per session (5). However, a study has shown that 1800 pulses can alter cortical excitability more permanently and induce expected cellular changes more effectively (18). In addition, an augmentation protocol based on iTBS has shown significant efficacy enhancement in the treatment of depression, and this protocol can significantly increase the response and remission rates of depressed patients by intermittently administering high-frequency pulsed stimulation (19). However, this augmentation protocol has not yet been applied to patients with schizophrenia. A systematic review suggests that iTBS may be an effective means of improving cognitive function and negative symptoms in patients with schizophrenia (20); however, the optimal therapeutic regimen remains to be explored.

Based on current evidence, we propose an augmented iTBS stimulation protocol for treatment of L-DLPFC based on cognitive function-related circuits in schizophrenia. We plan to deliver 1,800 pulses—three times the standard 600-pulse burst protocol—in order to provide robust, evidence-based data for evaluating the therapeutic efficacy of high-frequency rTMS on cognitive function. The core objective of this study is to validate the safety and efficacy of our proposed augmented iTBS protocol for the treatment of schizophrenia. With this study, we hope to demonstrate that augmented iTBS protocol can have a positive impact in several key areas, including Positive and Negative Syndrome Scale (PANSS) scores on clinical symptoms, Repeatable Battery for the Assessment of Neuropsychological Status (RBANS) on cognitive functioning, and functional near-infrared spectroscopy (fNIRS) on neuroimaging, while we will monitor serious adverse events (SAE) to assess safety.

## Method

2

### Participant

2.1

We are preparing a double-blind, sham-controlled research project with two randomized subgroups aimed at investigating the clinical effectiveness of a augmented iTBS protocol for the treatment of schizophrenia. Based on a recent meta-analysis of frontal cortex rTMS for improvement of schizophrenia (21), we assumed an effect size of 0.64. Using this assumption and the baseline values as covariates, we concluded that with a power equal to or greater than 80% (β= 0.20), there was a significant difference between the two groups in terms of improvement in cognitive function (α = 0.05), a sample size of 62 calculated using G*Power, and we expected a dropout rate of 10%. Therefore, we plan to include 70 patients who met the DSM-V diagnostic criteria for schizophrenia. We will assign patients to the active stimulation and sham stimulation groups in a 1:1 ratio, and patients participating in the study will be given sequentially numbered patient codes to which the corresponding treatment modality (active or sham stimulation) will be assigned (**Figure 1**). The subjects for this study will be recruited from the inpatients of Zigong Mental Health Centre, who need to meet all the inclusion criteria and not meet any exclusion criteria.

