#### Primary outcome

2.7.1

Our primary outcome will be the mean change scores of cognitive function assessed using RBANS from baseline to the end of the treatment period. The RBANS, developed by Randolph in 1998, assesses five cognitive domains through 12 subtests, including Attention (Digit Breadth and Encoding Tests), Verbal (Picture Naming and Semantic Fluency Tests), Visual Breadth (Picture Copying and Line Orientation Tests), Immediate Memory (Vocabulary Acquisition and Story Repetition Tests), and Delayed Memory (Vocabulary Recall, Vocabulary Re-recognition, Story Recall, and Picture Recall Tests). We expect that patients receiving active stimulation will show significant improvements in performance on these tests, scoring higher on the total score of the RBANS than the sham stimulation group.

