### Statistical analysis of data

2.8

The normality of the measures will be assessed using the Shapiro-Wilk test. The Levene test will be used to assess the conformity of the variance of the measures. Two independent samples t-test will be used for measures that met normality. The Mann-Whitney U test will be used for measures that did not meet normality. Categorical variables will be analyzed using the chi-square test. Pearson’s correlation analysis will be used to explore the relationship between cognitive function improvement and changes in neural activity. P-value <0.05 will indicate a statistically significant difference.

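### The 62 patients in Section 2.1 match a one-sided 0.05 t-test that the protocol never declares; read as two-sided, the planned unadjusted test has about 70% power, not 80%, if 0.64 is on the change-score SD

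*Protocol article*

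**What the plan says.** Section 2.1 (Participant) gives the effect size: "we assumed an effect size of 0.64". It describes the calculation as made "Using this assumption and the baseline values as covariates", "with a power equal to or greater than 80% (β= 0.20"), for the claim that "there was a significant difference between the two groups in terms of improvement in cognitive function (α = 0.05"). The result is "a sample size of 62 calculated using G*Power, and we expected a dropout rate of 10" per cent, and the plan is to include 70 patients allocated 1:1.

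Section 2.1 does not name the G*Power procedure, the number of sides, the SD that standardises 0.64, or a correlation between baseline and follow-up.

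Section 2.7.1 (Primary outcome) makes the primary outcome the mean change in RBANS from baseline to end of treatment. It expects patients on active stimulation to end up "scoring higher on the total score of the RBANS than the sham stimulation group".

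Section 2.8 (Statistical analysis of data) plans a two-sample t-test, or a Mann-Whitney U test where normality fails. It names no covariate-adjusted analysis. Its decision rule is "P-value <0.05 will indicate a statistically significant difference".

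**The concern.** The article states its inputs and its result, so the sample size can be checked. The usual two-sided calculation for an effect of 0.64 needs clearly more than 62 patients. The covariates that Section 2.1 mentions do not appear in the analysis in Section 2.8. So the stated power may belong to a test other than the planned one.

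Readers rely on this figure when they interpret a null result. If power is about 70%, the trial would miss a true effect of the assumed size about 30% of the time, against the 20% that Section 2.1 implies. If one-sided 0.05 is the hidden basis, the false-positive rate in the favourable direction is twice that of a conventional two-sided 0.05 test, and the reader is not told.

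**Working it through.** **Inputs.** From Section 2.1: effect size 0.64, alpha 0.05, power at least 80%, 1:1 allocation, N = 62, dropout 10%, 70 enrolled. From Section 2.8: unadjusted two-sample t-test. Assumed: 0.64 is Cohen's d, so f = d/2 = 0.32 for two equal groups.

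**Formula, t-test.** Noncentrality = d × √(n₁n₂/(n₁+n₂)), df = n₁+n₂−2. Power is the noncentral-t probability beyond the critical value.

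**1. Reproducing 62.** With 31 per arm, noncentrality = 0.64 × √15.5 = 2.520 and df = 60.
- One-sided 0.05: critical t = 1.671, power 80.1%. With 30 per arm it is 79.0%. So 31 per arm (62) is the smallest balanced size that reaches 80%.
- Two-sided 0.05: critical t = 2.000, power 69.8%.

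**2. Two-sided t-test at other sizes, d = 0.64.**

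| Evaluable | Power |
|---|---|
| 62 (31 + 31) | 69.8% |
| 63 (31 + 32) | 70.5% |
| 70 (35 + 35) | 75.2% |
| 78 (39 + 39) | 79.7% |
| 80 (40 + 40) | 80.7% |

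The effect detectable with 80% power at 62 is d = 0.72. If the Mann-Whitney test is used on normal data (relative efficiency 3/π), 80% power needs about 84.

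**3. G*Power ANCOVA, f = 0.32, two groups, one covariate.** Noncentrality = f²N, df = 1 and N−3. At N = 62: 0.1024 × 62 = 6.349, power 69.8%. At N = 79: 8.090, power 80.2%. Entering a covariate at an unchanged f costs one degree of freedom and gives no gain, so it does not produce 62.

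**4. ANCOVA with a gain from baseline.** If 0.64 is on the raw-score SD, adjustment multiplies the residual SD by √(1−r²), so f = 0.32/√(1−r²), where r is the baseline-to-post correlation. The values of r are assumed, because the protocol gives none.

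| r | f | Two-sided power at N = 62 |
|---|---|---|
| 0.3 | 0.335 | 74% |
| 0.4 | 0.349 | 77% |
| 0.5 | 0.370 | 82% |
| 0.6 | 0.400 | 87% |

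Power reaches 80% at r of about 0.47 with 62 evaluable (0.45 with 63).

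**5. Scale of 0.64 for the planned change-score t-test.** The SD of a change score is the raw SD × √(2(1−r)), for equal SDs at both visits. The two scales coincide at r = 0.5. If 0.64 is on the raw-score SD, the effect on the change scale is 0.64/√(2(1−r)). At r = 0.6 this is 0.716, and two-sided power at 62 is 79%. At r = 0.7 it is 0.826, and power is 89%. At r = 0.4 it is 0.584, and power is 62%. The 69.8% in step 2 therefore holds if 0.64 is on the change-score SD, or if r = 0.5.

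**6. Dropout.** 62/0.90 = 68.9, so 70 covers the loss, and 70 × 0.90 = 63 evaluable. The inflation is not at fault.

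**The case against.** **Sidedness is not stated.** A reader might infer that the 80% is simply false. The documents do not go that far. The word difference is neutral, and Section 2.7.1 expects a direction. If one-sided 0.05 was meant, 80% is correct as computed. But an expected direction does not declare a one-sided test, and a plain t-test judged at P<0.05 is conventionally read as two-sided.

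**Other routes to 62.** It is tempting to say that only a one-sided test can give 62. That is too strong. Section 2.1 mentions baseline covariates, and a two-sided ANCOVA reaches 80% at 62 with r of about 0.47 if 0.64 is on the raw-score SD. That route is possible but undocumented: it needs a correlation that Section 2.1 does not state and an analysis that Section 2.8 does not plan. The one-sided t-test gives 62 with no added input.

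**The 70% is conditional.** This objection stands. The figure depends on the SD behind 0.64, as step 5 shows, so it must be quoted with that condition.

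**The source of the effect.** Section 2.1 says "Based on a recent meta-analysis of frontal cortex rTMS for improvement of schizophrenia (21), we assumed an effect size of 0.64". A reader might infer that 0.64 is not an effect on cognition. That depends on the cited meta-analysis, which is not at hand. The short description settles nothing either way, so the point is not made here.

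**Conclusion.** The concern holds in a limited form. The stated 80% is not what the planned test delivers on its conventional two-sided reading. Power is about 70% with 62 or 63 evaluable and 75% with all 70, against at least 80% stated. This rests on two assumptions: the test is two-sided, and 0.64 is Cohen's d on the SD of the RBANS change score. Reaching 80% on that basis would take 80 evaluable patients, or 79 with the G*Power ANCOVA at f = 0.32.

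Separately, and on no assumption, Sections 2.1 and 2.8 disagree: the sample size is said to use baseline covariates and the analysis uses none. The documents do not show which calculation was run, so this is an undisclosed basis and a mismatch between sections. They do not establish that the trial is underpowered whatever analysis is used.

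**What to change.** Enrolment stays at 70.

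1. In Section 2.1, state two-sided alpha 0.05, the G*Power procedure, and the SD to which 0.64 refers. For the unadjusted comparison, with 0.64 on the change-score SD, restate power as about 70% at d = 0.64 with 62 to 63 evaluable, and 80% at d of about 0.72.
2. In Section 2.8, make the primary analysis an ANCOVA of the RBANS total adjusted for baseline, as Section 2.1 assumes. Give its power over a stated range of correlations. If 0.64 is on the raw-score SD, the N = 62 figures in step 4 can be used: 74%, 77%, 82% and 87% for r = 0.3, 0.4, 0.5 and 0.6. Quoting ANCOVA power without this change would again describe a test that is not planned.
3. If one-sided 0.05 was intended, say so in both sections.

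The cost is an amendment to two sections, and no extra patients. Item 2 changes the primary analysis, so with recruitment under way it should be fixed before anyone sees unblinded outcome data. The stated power for the unadjusted test becomes less favourable.

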**Figure 1 f1:**
[figure not shown]
Flowchart.

Clinical and cognitive assessments, along with fNIRS measurements, will be conducted by an independent rater blinded to the treatment condition at two time points: baseline and post-intervention (day 10)(**Figure 2**).

**Figure 2 f2:**
[figure not shown]
Enrollment schedule, treatment, and outcome measures. MoCA, Montreal Cognitive Assessment; PANSS, Positive and Negative Syndrome Scale; RBANS, Repeatable Battery for the Assessment of Neuropsychological Status; fNIRs, functional near-infrared spectroscopy.

### Inclusion criteria

2.2

1) Meeting the diagnostic criteria for schizophrenia according to the Diagnostic and Statistical Manual of Mental Disorders, Fifth Edition; 2) Stable clinical status and taking antipsychotic medication: continuously taking a stable dose of antipsychotic medication for more than 4 weeks; 3) Age between 18 and 60 years; 4) Montreal Cognitive Assessment(MoCA) score of 19-25 (22), able to cooperate in completing the scale; 5) Right-handed.

### Exclusion criteria

2.3

1) Presence of any significant neurological disorder; 2) Presence of mental retardation; 3) History of seizures or presence of epileptic activity on baseline electroencephalogram (EEG) (subject to evaluation by clinical EEG and epileptologist); 4) Alcohol or drug abuse within the last 3 months; 5) Depressive episodes or antidepressant treatment within the last 4 weeks; 6) History of electroconvulsive therapy (ECT); 7) Have a pacemaker, drug pump, cochlear implant, defibrillator, neurostimulator, or other metal device implanted in the body that is incompatible with rTMS; 8) Presence of severe damage to the skin surface in the area of cranial stimulation; 9) Being pregnant; 10) Presence of a serious physical illness; 11) Presence of severe positive symptoms that may interfere with the administration of cognitive tests.

### Randomization

2.4

To ensure the scientific rigor and balance of sample allocation, this study will employ a stratified randomization method to evenly distribute 70 samples into two groups. The aim is to minimize the bias in sample allocation and enhance the reliability and reproducibility of the experimental results. Gender is an important potential confounding factor that may influence the study outcomes. Therefore, the samples will be stratified by gender into two layers: the male stratum and the female stratum. Within each stratum, a random number generator will be used to assign a random number to each sample. The random numbers will be generated following a uniform distribution ranging from 0 to 1. Subsequently, the samples within each stratum will be sorted based on the magnitude of the random numbers. The first 50% of samples within each stratum will be allocated to the active stimulation group, while the remaining 50% will be allocated to the sham stimulation group.

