## Trail status

4

The protocol version number is V1.0, and the date is July 23, 2025. The Ethics Committee of Zigong Mental Health Center approved the study protocol on August 2,2025(approval number 20250802). The trial was registered on August 21,2025(ChiCTR2500107943). The trial started on September 1, 2025. The trial is currently recruiting participants. We predict that the recruitment will be completed by January 31, 2026.

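### The allocation rule in Section 2.4 needs each gender stratum to be complete before anyone is allocated, which does not fit sequential enrolment without stated stratum sizes, so the even split is not assured

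*Protocol article*

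**What the plan says.** Section 2.4 (Randomization) sets the aim: "this study will employ a stratified randomization method to evenly distribute 70 samples into two groups". It then gives a complete algorithm:

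- Strata: "the samples will be stratified by gender into two layers: the male stratum and the female stratum".
- Each member of a stratum receives a uniform random number between 0 and 1.
- Ordering: "the samples within each stratum will be sorted based on the magnitude of the random numbers".
- Allocation: "The first 50% of samples within each stratum will be allocated to the active stimulation group", and the remainder goes to sham.

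Section 2.1 (Participant) describes allocation differently. The ratio is 1:1, with treatment tied to a code issued in sequence: "patients participating in the study will be given sequentially numbered patient codes to which the corresponding treatment modality (active or sham stimulation) will be assigned".

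Section 4 (trial status) dates the start to 1 September 2025 and predicts the end of recruitment by 31 January 2026. It adds: "The trial is currently recruiting participants".

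The article gives no size or quota for either stratum, no list length, and no rule for a stratum with an odd number of patients.

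**The concern.** Ranking needs a closed set. Whether a man is in the first half of the male stratum cannot be known until every man has a number. In this trial patients arrive over about five months and each is assessed again at day 10 (Section 2.1). The article does not say that treatment waits until all 70 are enrolled. Taken as a rule for sorting enrolled patients, Section 2.4 therefore does not fit the enrolment that Sections 2.1 and 4 describe.

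The site must then be using some workable version of the rule, and the article does not say which. Two things are at stake. One is the even split overall and within gender, which is the stated purpose of the method. The other is whether a reader of the results can tell how patients were actually allocated. The trial is already recruiting, so some patients may have been allocated by a procedure other than the published one.

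**Working it through.** **Inputs.** From the article: 70 patients, 1:1, two gender strata (Sections 2.1 and 2.4), and an assumed effect size of 0.64 with α = 0.05 (Section 2.1). Assumed here: a male share of 50–70%, because the article gives no gender split. No figure in the article is in dispute; its target is 70/2 = 35 per arm.

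**Reading 1: sort the enrolled patients.** Nobody can be allocated until the stratum closes. This conflicts with the dates in Section 4 unless treatment waits, which is not stated.

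**Reading 2: pre-numbered slots with a fixed gender quota.** Each stratum is one large block. Balance is exact if the quota is even and filled exactly. Someone who knows the quota and all past allocations, and always guesses the arm with more places left, is right at a rate of [n + (4ⁿ/C(2n,n) − 1)/2]/2n for a stratum of 2n. For 2n = 36 this is [18 + (7.57 − 1)/2]/36 = 0.59, against 0.50 by chance. On average the last 2n/(n + 1) = 36/19 ≈ 1.9 allocations per stratum are certain to that person.

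**Reading 3: pre-sorted lists built on guessed totals.**

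- *Lists too short.* Suppose lists of 35 are made for each gender, and 45 men and 25 women enrol (illustrative). The male list runs out 10 patients early. The female list is left unfinished, so the number of active women varies around 12.5 with SD √(25 × 0.25 × 10/34) = 1.36.
- *Lists long enough for any split.* Take 70 slots per gender, half active, in random order, used until 70 patients are enrolled. With M men, each list contributes a variance of 0.25 × M(70 − M)/69 to the number of actives. For M = 42 the SD of total actives is √(2 × 0.25 × 42 × 28/69) = 2.92. The SD of the arm difference is twice that, 5.84, and the mean absolute difference is about 0.80 × 5.84 ≈ 4.7. Simulation with M varying gives:

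| Assumed male share | Mean arm difference | Chance of 30:40 or worse |
|---|---|---|
| 50% | 4.7 | 13% |
| 60% | 4.6 | 12% |
| 70% | 4.3 | 9% |

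**Reading 4: use the list in its sorted order.** Section 2.4 does not say that codes are dispensed in any order other than the sorted one. If they follow it, the first half of each stratum is all active and the second half all sham. Allocation is then fully predictable and confounded with calendar time.

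**Reading 5: treat each number below 0.5 as active.** This is simple randomisation. The mean arm difference is 6.7 and the chance of 30:40 or worse is 28%.

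**Comparator.** Gender-stratified permuted blocks of random size 4 and 6, at a 60% male share, gave a mean arm difference of 0.9 and a maximum of 6 in 10,000 simulated trials.

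**Power.** For a two-sided t-test at d = 0.64 and N = 70, the noncentrality is 0.64 × √(n₁n₂/70). At 35:35 this is 2.68 and power is 75.2%. At 30:40 it is 2.65 and power is 74.3%. The difference is about 1 percentage point.

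**The case against.** The strongest reply is that the rule was never meant for enrolled patients. If its units are pre-numbered slots, random numbers and sorting generate the list, the sequential codes in Section 2.1 dispense it, and the two sections agree. That reading is workable, so a reader should not conclude that the rule cannot be run at all. It needs fixed stratum sizes, however, and the article gives none while recruiting a gender mix it cannot know in advance. List lengths and the custody of the list may sit in the full protocol, and their absence is not counted here. The fault is that the algorithm the article does state does not fit the enrolment it describes.

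A reader might also infer that staff can foresee allocations and steer who enters. The treating researcher does know the arm, because sham is delivered by turning the coil (Section 2.6). But Section 2.5 keeps that person out of assessments, and nothing says that this person recruits or passes allocations on. Nor can sorting in small batches be charged with predictability: if a batch is fully enrolled before it is sorted, no entry decision is left to influence. Guess rates such as 75% or 71% for blocks of 2 or 4 describe blocks filled one patient at a time, and so are not evidence against this rule.

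The same measure also counts against the remedy. With blocks of 4 and 6 and 35 patients per stratum (assumed), someone who knows past allocations guesses about 69% correctly, against 59% for one block per stratum. That part of the objection stands. The case for blocks rests on balance and on being usable with sequential entry, and protection from guessing has to come from concealment.

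**Conclusion.** The point holds in a limited form. As written, Section 2.4 needs complete strata, while Sections 2.1 and 4 describe sequential entry with no stratum sizes. Only a slot-based reading with fixed gender quotas makes the rule work as stated, and the article does not supply those quotas.

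Without quotas the stated even split is not assured. With 70-slot lists, the typical arm difference is 4 to 5 patients and the chance of 30:40 or worse is 9–13%, against a mean difference of about 0.9 under stratified blocks. These figures rest on the assumed male share and on the version of the rule that is used, which the article does not show.

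The loss of power is minor (75.2% to 74.3%). Selection bias is a possibility under some readings, notably dispensing in sorted order, and the article does not show that it is occurring. The matter still deserves correction now, because allocation underpins the whole comparison and patients are already being enrolled.

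**What to change.** Replace the rule in Section 2.4 with a computer-generated list prepared in advance, stratified by gender, in random permuted blocks of undisclosed varying size. Make each gender's list long enough for any split of the 70. Dispense it in order through the sequential codes of Section 2.1, concealed from those who recruit, and reword Sections 2.1 and 2.4 so that they describe one procedure. Document how patients already enrolled were allocated, and report this with the results.

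The cost is a short amendment and a few hours of programming; the sample size stays at 70. There are two downsides. Incomplete last blocks leave a slight imbalance. Small blocks are also themselves guessable by anyone who knows past allocations, so the list and the past allocations must be kept from recruiting staff.
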